## Discussion

The study aims to evaluate whether implementation of medication monitors with daily remote monitoring and differentiated care is able to increase the proportion of patients with ≥ 80% adherence to drug sensitive TB treatment. Although medication monitors have been used to measure adherence in HIV treatment patients, this study is among the few studies investigating adherence using medication monitors among drug-sensitive TB patients in sub-Saharan Africa [17]. The study is also one of the first to evaluate differentiated care following information from an adherence technology. The medication monitor offers a real time documentation of medication intakes, which allows ability to monitor medication adherence whenever required. This approach will also allow for a further discussion of why non-adherence occurred when participants return to facility for refills. The differentiated care approach enables staff to follow-up on a weekly basis on participants that have missed doses allowing for timely action on missed doses unlike waiting for patients to return to facilities at end of the month as it is currently done in routine practice. The approach will also assist us in identifying people with TB who may need more support when on TB treatment.

Other digital adherence technologies that have been explored for TB medication adherence include 99-DOTS, which requires patients to give a missed call to a toll free number when the pills are removed from the medication blister pack when taking a dose. The disadvantage of using 99-DOTS is that treatment support before treatment intake is not provided but only done once a patient misses a dose [9]. Another technology that has been explored is video-supported treatment where patients take a video of themselves ingesting TB treatment and sending it to health care providers to view later [18]. The disadvantage with using this technology is that it requires that a patient have a smartphone and have access to Internet connection. Other criticisms have been that it is an intrusive and patronising method. Both these technologies require some effort from the patient to either give a missed call, send an SMS to the toll free number for 99-DOTS, or take a video of themselves ingesting medication. Furthermore, 99-DOTS sleeves have to be customised to the different medication blister packs.

The advantages of the medication monitor over the other technologies is that it has both visual and audio medication reminders and monthly refill reminders. The monitor software also automatically sends text messages to patients if a patient does not take their medication at the scheduled time. All these features attempt to support patients when taking treatment [19]. With differentiated care based on adherence monitoring, one may be able to counter issues, related to fear of side effects, lack of disclosure, lack of support, etc., through additional motivational counselling.

There are some operational challenges that need to be overcome to implement the study. To implement the intervention, staff need access to a computer/portable device to be able to assign a device to a patient. Having a computer in the TB consultation rooms is not the current practice in South Africa and we will therefore provide electronic tablets loaded with data to our study team so this can be done. The research team is operationalising the intervention and they require cell phones and airtime to be able to call patients who missed their doses, these will also be provided by the study. The configuring of each device also requires access to an Internet connection. Most facilities in South African do not have free Internet access available and the study must therefore provide data to the study team. Reports that will be used to implement the differentiated care will not be automatically generated, so a dedicated person needs to download and generate them weekly. One of the study staff per province will be responsible for ensuring that this is done. During the follow-up period that patients are still taking their TB treatment, we run a risk of some patients losing their medication monitors. If this occurs, the study will replace the medication monitors.

### Limitations

One limitation of the study is that intake notification through opening of the box does not mean that a patient has ingested their medication. We might get instances where the system has recorded an opening as an intake but the patient has not ingested the medication and vice versa. We will not perform plasma or urine drug concentration tests to check objectively on dosing. However, there is evidence in HIV patient populations in South Africa that electronic adherence monitoring monitors are a good measure for adherence [20].

A second limitation is that most TB patients in South Africa have HIV co-infection but the current study is not monitoring medication adherence for both diseases. While the differentiated care strategy is labour intensive, the study will allow us to evaluate which elements are more feasible and practical and which are more effective. The HIV community in the country is already using a differentiated care model to address non-adherence in patients [21]; therefore, use of this approach in TB care might bring opportunities for integrated patient management. We are assuming high levels of acceptability of the medication monitor; this will be assessed in the qualitative aspects of the study. This might also introduce some population selection bias in our study as only people that are willing to use the medication monitor will be enrolled and not everyone with TB who are started on TB treatment in the facilities that we are recruiting from.

### Strengths

The strength of this study is that it is a pragmatic trial, taking place in 18 clinics across three provinces of South Africa reflecting rural and urban settings, with varying TB and HIV burdens. In addition, the study is being conducted within the routine programme and care is likely to be influenced by the routine setting, although research staff may support some activities. We are using trained lay workers to educate participants about their treatment, which is a strength, and if found to be successful, the intervention could be implemented without requiring specialist highly trained staff. The inclusion of the socio-behavioural and economic evaluations will allow implementation issues to be explored allowing for easier implementation if the intervention is found to be successful.

### Dissemination

Our study findings will be shared with the facility managers and district officials where the study took place, as well as provincial and national Department of Health stakeholders. The study is part of the national DISRUPT TB Innovations Consortium in South Africa through which results will be shared with other TB researchers, non-governmental organisations, and provincial and national stakeholders. In addition, findings will be disseminated in both local and international conferences, and published in peer-reviewed journals. Authorship on publications generated for this trial will be granted to individuals who have contributed substantively to the design, conduct, and interpretation of trial findings as well as reporting of the trial. A de-identified participant-level dataset will also be made available after journal publication.

## Conclusions

The current study will report on the feasibility, acceptability, and cost-effectiveness of using remote medication monitors with a differentiated care approach to support DS-TB patients within the South African context. If this intervention is successful, a larger implementation project will be needed to further understand the implementation challenges of rolling out the intervention at a wider scale.

## Trial status

The protocol is version 5.0, dated 25 February 2020. The trial started recruitment on 17 May 2019. The recruitment to trial is ongoing until December 2020 and follow-up is expected to be completed on 30 December 2021.

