### Study population and eligibility criteria

The study is recruiting all adults aged ≥18 years and children aged 2–17 years with clinically or microbiologically diagnosed DS-TB. The inclusion criteria include initiating TB treatment within the last 14 days, adults and caregivers of children who are willing and able to provide informed consent, and children aged 7–17 years old who are willing and able to provide informed assent. Patients need to be willing to use the medication monitor; agree to be followed-up with text messaging, phone calls, and home visits; live within the study catchment area; and be willing to inform the study team of any change of address during the treatment as well as follow-up period. We expect to enrol approximately 2610 DS-TB patients and follow them up for 18 months post enrolment. The study started enrolment in May 2019 and will complete follow-up in December 2021. This manuscript could not be submitted for consideration before enrolment commenced as the methodology had to piloted and refined during the early phases of the enrolment period.

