#### Follow-up

Follow-up of all patients in intervention and standard of care arms continues every 3 months until 12 months after completion of treatment (approximately 18 months after enrolment) (Table 1). Patients who die, declared as loss to follow-up during treatment by facility staff, or move out of our study area will be withdrawn from study. At each follow-up visit, TB symptom screening will be performed and, if required additional investigations such as sputum tests, will also be conducted. Patients are reimbursed ZAR 50 for travel costs for each visit. All patients are requested to provide sputum specimens for culture testing at 6 months from enrolment and 12 months post TB treatment completion (18 months from enrolment).

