### Study outcomes’ definitions

Treatment completed is defined as patient who has completed their treatment without evidence of failure but without any record of a negative smear or culture result in the last month of treatment or any time in previous occasion.

Cured is defined as pulmonary TB patient with a positive smear, Xpert MTB/Rif or culture result (bacteriologically confirmed TB) at the beginning of treatment who has a negative smear microscopy or culture result at the last month of treatment.

Lost to follow-up is defined as a patient whose treatment has been interrupted for more than 2 months.

Treatment failed is defined as a patient whose sputum smear or culture is positive at month 5 or later during treatment.

TB recurrence is defined as a patient with a positive culture result at any time during the 12 months follow-up period post treatment completion.

Unfavourable outcome at 18 months post enrolment is defined as treatment failure, lost to follow-up and death during treatment, and recurrence after end of treatment.

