### Sample size considerations

Sample size calculations were conducted accounting for the clustered design [16]. Throughout we have assumed a harmonic mean of 145 TB patients/cluster, nine clusters per arm and a two-sided type I error of 5%.

Proportion with >80% adherence: Assuming a percentage with non-adherence in the standard of care arm of 30% and coefficient of variation of variation of 0.12, we will have 90% power to detect a 40% reduction in the endpoint in the intervention arm. For a successful outcome at the end of treatment of 80% in the standard of care arm and a coefficient of variation of 0.06, we will have 90% power to detect an increase to 90%. For unfavourable outcome 18 months after enrolment (defined as on-treatment lost to follow-up, death, treatment failure, and recurrence) of between 13 and 20% in the standard of care arm and a coefficient of variation of 0.25, we will have at least 80% power to detect a 40% reduction in the intervention arm.

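### Recruiting to December 2020 with 18 months of follow-up cannot finish on 30 December 2021, so recurrence in the 18-month secondary endpoint would be incompletely observed for late enrolees

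*Protocol article*

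**What the plan says.** The protocol article gives calendar dates in two places. Trial status states "The trial started recruitment on 17 May 2019" and then "The recruitment to trial is ongoing until December 2020 and follow-up is expected to be completed on 30 December 2021". Study population and eligibility criteria repeats the end date: "The study started enrolment in May 2019 and will complete follow-up in December 2021".

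The follow-up per participant is also given more than once. Study population and eligibility criteria says "We expect to enrol approximately 2610 DS-TB patients and follow them up for 18 months post enrolment". The Follow-up section runs three-monthly visits to 12 months after treatment ends, which it equates with about 18 months from enrolment, and Table 1 has a month-18 column. On cultures, the Follow-up section says "All patients are requested to provide sputum specimens for culture testing at 6 months from enrolment and 12 months post TB treatment completion". In Table 1, sputum at months 9, 12 and 15 is taken only if symptoms are reported.

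The endpoint that depends on this follow-up is secondary: "Unfavourable outcome at 18 months post enrolment is defined as treatment failure, lost to follow-up and death during treatment, and recurrence after end of treatment". Recurrence means a positive culture in the 12 months after treatment completion. For this endpoint Sample size considerations assumes 145 patients per cluster, nine clusters per arm, a control rate of 13 to 20% and a coefficient of variation of 0.25, and concludes that "we will have at least 80% power to detect a 40% reduction in the intervention arm".

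**The concern.** The last recruitment month and the last follow-up day are about 12 to 13 months apart, but each participant is owed about 18. The article neither reconciles the dates nor mentions administrative truncation.

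If both dates are followed, participants enrolled in the second half of 2020 never have the month-18 visit. That visit is the one occasion after the end of treatment when everyone gives sputum, so recurrence without reported symptoms could go undetected in this group. The later part of their recurrence window is also unobserved. If clinics recruit at different speeds, the truncated share would differ between clusters, and the planned analysis compares cluster-level summaries. The power statement uses the same 145 per cluster for every endpoint and makes no allowance for incomplete month-18 follow-up.

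**Working it through.** **1. Dates** (Trial status; Study population and eligibility criteria; Follow-up)

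- December 2020 + 18 months = June 2022, against a stated end of 30 December 2021.
- 30 December 2021 − 18 months = 30 June 2020, the latest enrolment date compatible with month 18.
- Follow-up available to the last enrolee is 12.9 months if recruitment closes on 1 December 2020 and 12.0 months if it closes on 31 December.
- With treatment ending about 6 months after enrolment, those last enrolees have about 6 to 7 of the 12 months of recurrence follow-up.

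**2. Share affected.** The article gives no accrual curve, so uniform accrual from 17 May 2019 is an assumption.

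- Close on 1 December 2020: 564 days in all, 154 of them after 30 June 2020; 154/564 = 27.3%, about 713 of 2610.
- Close on 31 December 2020: 594 days, 184 of them after 30 June 2020; 184/594 = 31.0%, about 809 of 2610.

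**3. The article's own power.** The unmatched cluster-trial formula for proportions, solved for power, is

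power = Φ( √[ (c − 1)(p0 − p1)² / V ] − 1.96 ), with V = p0(1 − p0)/m + p1(1 − p1)/m + k²(p0² + p1²).

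Inputs from Sample size considerations: c = 9, m = 145, k = 0.25, and p1 = 0.6 p0 for a 40% reduction.

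- p0 = 0.13, p1 = 0.078: V = 0.000780 + 0.000496 + 0.001437 = 0.002712. √(8 × 0.002704 / 0.002712) = 2.824. Power = Φ(0.864) = 80.6%.
- p0 = 0.20, p1 = 0.12: V = 0.001103 + 0.000728 + 0.003400 = 0.005232. √(8 × 0.0064 / 0.005232) = 3.128. Power = Φ(1.168) = 87.9%.

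The stated figure therefore reproduces. At 13% it needs at least 141 evaluable patients per cluster (143 with a t distribution on 16 degrees of freedom), so only 2 to 4 per cluster can be spared.

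**4. Worst case: all late enrolees excluded.** m = 145 × 0.69 = 100, or 145 × 0.73 = 105.8.

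| Control rate | m = 145 | m = 105.8 | m = 100 |
|---|---|---|---|
| 13% | 80.6% | 74.1% | 72.8% |
| 15% | 83.4% | 77.7% | 76.5% |
| 17% | 85.5% | 80.5% | 79.4% |
| 20% | 87.9% | 83.7% | 82.8% |

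Power returns to 80% at a control rate of about 16.7% (27% excluded) to 17.5% (31% excluded).

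**5. Late enrolees kept, with some recurrences missed.** Let f be the late share, s the recurrence share of the endpoint and L the fraction of late enrolees' recurrences missed. Both event rates are multiplied by 1 − f·s·L, with m = 145. The article gives neither s nor L; the ranges tried were s = 0.2 to 0.5 and L = 0.25 to 1.

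- Control rate 13%: 80.3% (s = 0.2, L = 0.25) down to 76.9% (f = 0.31, s = 0.5, L = 1).
- Control rate 20%: 87.7% down to 85.4%.

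**6. Sensitivity to the formula.** Using c in place of c − 1 is less conservative. At 13% it starts at 85.0% and falls to 77.7 to 78.9% under exclusion. In the least favourable case of step 5 (p0 = 0.10985, p1 = 0.06591, V = 0.002125) it gives Φ(√(9 × 0.001931 / 0.002125) − 1.96) = Φ(0.90), about 82%. The shortfall under exclusion at 13% therefore appears with either form. The shortfall with late enrolees kept appears only with the c − 1 form.

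**The case against.** The strongest reply is that the article fixes follow-up per participant at about 18 months in several places, while the end date is an expectation in a status section. A single outdated calendar date would explain the conflict with nobody truncated. That is possible, and the document cannot settle it. But the end date appears in two sections, and neither the word approximately nor the 14-day enrolment window can absorb a gap of 5 to 6 months. The passages still have to be reconciled.

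A reader might infer three stronger things that the document does not support.

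- **That the stated power is lost.** Even excluding every late enrolee leaves about 83 to 84% at a 20% control rate. Exclusion is also harsher than the design requires: each late enrolee has at least about 12 months, which covers on-treatment loss to follow-up, death and failure, the month-6 culture, and some months of symptom-driven recurrence testing.
- **That participants without a month-18 visit will be coded as having no event.** Data management and analyses says only that a binary variable will be generated. It does not say how an unobserved month-18 status is coded, and the detailed analysis plan is not shown. Such coding is a risk to close off, not a stated rule.
- **That about 30% of participants are certain to miss month 18.** That share rests on uniform accrual and on both dates being literally correct.

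**Conclusion.** The contradiction in the dates is certain and needs no assumption. If recruitment and follow-up run exactly as dated, everyone enrolled after 30 June 2020 lacks the month-18 visit, and recurrence within the 18-month composite is incompletely ascertained for them. The size of that group, about 710 to 810 of 2610, depends on uniform accrual and could be smaller or larger.

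The effect on power is conditional. The claim of at least 80% is not assured towards the lower end of the 13 to 20% range, where it has almost no slack, and it stands at the upper end. The figures for late enrolees kept in the analysis rest on assumed recurrence shares.

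The consequence is confined to this secondary endpoint. Primary adherence is measured during treatment, and treatment success is judged by 210 days, which for a December 2020 enrolee falls by about the end of July 2021.

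**What to change.** Reconcile Trial status and Study population and eligibility criteria with the Follow-up section and Table 1. The simplest change is to set the end of follow-up at 18 months after the last enrolment, about June 2022. It costs a corrected date and up to about six more months of visits that the schedule already promises.

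If 30 December 2021 cannot move:

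- keep late enrolees in the analysis for the on-treatment components;
- state that recurrence is not fully observed for them, and do not count them as recurrence-free; for example, analyse recurrence by time to event or person-time, with a sensitivity analysis in those enrolled by 30 June 2020;
- qualify the power statement at the lower control rates, using the actual accrual.

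This costs a short paragraph and a less favourable power statement. It should be settled before the 18-month outcome is analysed.

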## Data Availability

Not applicable

## Abbreviations

Medication monitor: Wisepill evriMED 1000 device
TB: Tuberculosis
DS-TB: Drug-susceptible TB
